### Cancer cachexia in elderly cancer patients

The population of elderly cancer patients has been increasing due to a general increase in life expectancy. According to the Surveillance, Epidemiology, and End Results database, more than half of those diagnosed with lung cancer were people older than 70 years [13]. Elderly patients already have reduced physiological skeletal muscle and nutritional status due to aging, resulting in many elderly patients being diagnosed with cancer cachexia. We previously reported that cancer cachexia in elderly patients is strongly associated with decreased activity of daily living (ADL) scores and longer hospitalizations [14]. Furthermore, skeletal muscle depletion during chemotherapy has a negative impact on physical function in elderly non-small cell lung cancer (NSCLC) patients [15]. Because elderly patients independently have a high risk of falls and fractures, careful intervention is necessary for elderly patients with body weight loss and weak skeletal muscle. It is well known that elderly cancer patients are at risk for malnutrition, including cachexia, and they are very fragile when performing daily activities. Therefore, we selected elderly patients with refractory cancer as the participants in this study to investigate multimodal interventions for cachexia, including exercise and nutritional intervention.

### Results from early-phase prospective trial: the NEXTAC-ONE study

We reported a phase I study to evaluate the feasibility of multimodal interventions, including exercise and nutritional intervention, for elderly patients with advanced NSCLC or pancreatic cancer [16]. That study was named the “NEXTAC (Nutrition and Exercise Treatment for Advanced Cancer)-ONE” study and was performed as a prospective single-arm study to assess the feasibility of early nonpharmacological, multimodal interventions (NEXTAC program). The NEXTAC program was designed specifically for elderly cancer patients with high cachectic potential, and it consists of nutritional sessions, exercise educational sessions (muscle training and physical activity), lifestyle consultations and daily oral nutritional supplements (Inner Power®) that were implemented over an 8-week study period. We hypothesized that it is possible to initiate the NEXTAC program in the early treatment phase in elderly patients with advanced cancer, and we conducted the phase I study. The primary endpoint of the study was the participation rate, which was measured at three points during the 8-week study period. The three assessment points were as follows: at the time of study entry and 4 ± 2 weeks and 8 ± 2 weeks after the intervention started. In addition to the participation rate in the NEXTAC program, the physical activity level of each participant was evaluated using an accelerometer. The primary endpoint of the NEXTAC-ONE study was feasibility, which was defined as the proportion of participants attending ≥4 of 6 sessions. In total, 6 pancreatic cancer patients and 24 NSCLC patients were enrolled. The median age was 75 (range, 70–84) years. In total, 29 patients participated in more than 4 of the 6 sessions (96.7, 95% confidence interval; 83.3–99.4%) and did not experience serious adverse events related to these interventions. This phase I study met the primary endpoint, and we showed a high attendance rate and satisfactory safety profile for the NEXTAC program, with high compliance rates with regard to consuming the supplements, completing the diaries, and wearing the pedometers/accelerometers. Additionally, the results suggested that the NEXTAC interventions might induce behavioral changes, with consequent improvement in the patients’ QOL [17].

### Aim of the NEXTAC-TWO study

Based on the results of the NEXTAC-ONE study, we hypothesize that early nutritional and exercise interventions with lifestyle consultations will be feasible and will help maintain physical activity levels in elderly patients with advanced cancer who are at high risk of cachexia. We are conducting a randomized trial to elucidate whether the nonpharmacological, multimodal intervention (NEXTAC program) prolongs survival without disability in elderly patients with advanced NSCLC or pancreatic cancer.

The target population of this study is elderly cancer patients. We previously reported that compared with patients without cachexia, cachexic patients have an increased risk of prolonged hospital stays and higher medical costs [14]. It is well known that elderly patients are at high risk for cachexia. The prevention of the progression of cachexia in elderly patients has the potential to not only improve the QOL but also to reduce their medical expenses. There are several established nonpharmacological interventions for community-dwelling elderly populations that are designed to prevent sarcopenia, disability, or falls [18, 19]. This study will be helpful in designing new strategies to prevent cachexia in elderly cancer patients.

### Translational research of the NEXTAC-TWO study

We are also conducting a translational study to investigate new biomarkers for the diagnosis of cachexia. There is increasing evidence of a close link between cancer cachexia and plasma free amino acid (PFAA) or ghrelin levels [20, 21]. Cancer cachexia is characterized by skeletal muscle loss and anorexia [22]. Low levels of PFAAs reflect the depletion of the protein reserve by cachexia-induced skeletal muscle loss in a murine cachexia model using human pancreatic cancer cells. A low active ghrelin ratio is related to severe appetite loss in patients with advanced pancreatic cancer. This translational research aims to characterize PFAAs and plasma ghrelin levels in cancer cachexia patients.

## Methods

### Study design and participants

The NEXTAC-TWO study is a multicenter, randomized phase II study with 130 participants allocated 1:1 to an intervention group or a control group. One hundred thirty patients will be recruited from 15 Japanese institutions according to the inclusion criteria and exclusion criteria listed in Table 1. Participating institutions include public hospitals, university hospitals, and cancer centers in Japan. The list of study institutions is available in Additional file 2. Recruitment began in August 2017 and is expected to be completed in July 2020.

**Table 1 Tab1:** Inclusion and exclusion criteria

Inclusion Criteria	
1) Diagnosis of advanced non-small cell lung cancer or inoperable pancreatic cancer	
2) Scheduled for systemic cancer therapy (i.e. chemotherapy, and/or targeted therapy and/or immunotherapy)	
i. In pancreatic cancer patients, planned systemic chemotherapy only allows of the combination of gemcitabine with nanoparticle paclitaxel.	
3) Eastern Cooperative Oncology Group (ECOG) performance status 0 to 2	
4) Age ≥ 70 years	
5) Body weight of 6 month ago can be confirmed	
6) An expected survival of ≥3 months as judged by investigators	
7) Written informed consent	
8) Adequate organ function	
i. Hemoglobin ≥8.0 g/dl	
ii. Total bilirubin ≤2.0 mg/dl	
iii. Aspartate aminotransferase ≤150 IU/L	
iv. Alanine aminotransferase ≤150 IU/L	
v. Serum creatinine ≤2.0 mg/dl	
vi. Arterial oxygen saturation (SpO_2_) ≥ 90% or partial pressure of oxygen in arterial blood (PaO_2_) ≥ 60 Torr in room air	
vii. Resting heart rate < 120 beat per minute	
Exclusion criteria	
1) Patients received prior chemotherapy except adjuvant chemotherapy	
2) Active malignancy requiring cancer treatment including chemotherapy, radiotherapy and surgery within 3 months	
3) Patients who need nursing care at following situation (based on Katz Index)	
i. Bathing	
ii. Dressing	
iii. Transferring	
iv. Feeding	
4) Symptomatic brain metastasis or leptomeningeal carcinoma	
5) Bone metastasis with high risk of fracture	
6) Patients who are difficult to evaluate or intervene with cardiovascular disease, bone and joint disease, neuromuscular disease etc.	
7) Patients who are difficult to participant due to psychiatric disorder	
8) Patients who are difficult to oral intake	
9) History of acute myocardial infarction, unstable angina, uncontrollable hypertension, and symptomatic sustained arrhythmia within 6 months. Stable atrial fibrillation treated with appropriate anticoagulation therapy is allowed.	
10) Uncontrollable diabetes mellitus	
11) Patients whose appropriate period has not passed since prior treatment	
i. Surgery: 7 days	
ii. Palliative radiation: 1 day	
iii. Minor surgery (i.e. biopsy): 1 day	
12) Screening failure	
i. Patients who failed to wear the accelerometer for more than 4 days	
ii. Patients who could not properly handle the accelerometer	
iii. Patients who failed to initiate first-line therapy within 14 days of enrollment	

This study consisted of two periods, namely, the screening period and the study period (Fig. 1). In the screening period, after written informed consent is obtained, the investigator educates the eligible patients regarding the wearing and handling of an accelerometer. Patients who demonstrated their ability to wear and handle the accelerometer for at least 4 days are enrolled and randomized. If the patients cannot wear the accelerometer or the investigator determines that the patient is not able to handle the accelerometer adequately, the patient is judged to be ineligible and is not enrolled in the study. The study period is defined as the time between the date of study enrollment and the date of the occurring disability event or death.

**Fig. 1 Fig1:**
[figure not shown]
Study Schema: this study is consisted of two periods; screening period and study period

### Assessments and interventions

The details of the assessment and exercise program in the NEXTAC-TWO study are shown in Table 2. There are no restrictions in concomitant care or interventions in both intervention and control group. No provision for ancillary or post-trial care is planned.

**Table 2 Tab2:** Assessments and interventions

			Control arm			Intervention arm		
Sessions		Time point^a^	T1	T2/T3	T4	T1	T2/T3	T4
		Detail of assessment/intervention						
Nutritional sessions 30 min at T1 20 min at T2, T3, and T4	Assessments	•Food intake	○	–	○	○	○	○
		• Nutritional status (MNA^d^)	○	–	○	○	○	○
		• Nutritional checklist^b^	○	–	○	○	○	○
		•Skeletal muscle analysis	○	–	○	○	–	○
		•Diet diary collection	–	–	–	–	○	○
	Interventions	• Nutritional advice	–	–	–	○	○	○
		• Support for NIS^d^ management, food environment, and eating-related distress	–	–	–	○	○	○
		• ONS^d^ prescription^c^	–	–	–	○	○	–
Exercise session 30 min at T1 20 min at T2, T3, and T4 each for A and B.	Assessments	• Assessment of physical function (Hand-grip strength, SPPB^d^)	○	–	○	○	–	○
		• Exercise diary collection	–	–	–	–	○	○
		• Assessment of physical activity (Physical activity measurement, Physical activity interview)	○	–	–	○	○	○
		• EORTC-QLQ-C30 questionnaire	○	–	○	○	–	○
	Interventions	A. Home-based resistance training						
		• Prescription (T1) and modification (T2, T3, T4) of exercise program	–	–	–	○	○	○
		• Instruction of exercise procedures	–	–	–	○	○	○
		•Education of self-modification	–	–	–	○	○	○
		B. Physical activity promotive counseling						
		• Prescription of target daily step	–	–	–	○	○	○
		• Physical activity counseling	–	–	–	○	○	○
		• Education of fall prevention	–	–	–	○	○	○

^a^Baseline assessments were performed during the time between study entry and initiation of chemotherapy (T1 point). Subsequent assessments were at 4 ± 2 (T2 point), 8 ± 2 (T3 point), 12 ± 2 (T4 point) weeks after the study enrollment

^b^Nutritional checklist to collects information about presence or absence of nutrition impact symptoms, problems in food environment, or eating-related distress

^c^A branched-chain amino-acids rich oral nutritional supplement (Inner Power®, Otsuka Pharmaceutical Co., Ltd., Japan) was provided one pack daily for 12 weeks

^d^*MNA* Mini-nutritional assessment, *NIS* nutrition impact symptoms, *ONS* oral nutritional supplement, *SPPB* Short Physical Performance Battery

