#### Time points of assessments and interventions

Exercise and nutritional assessment data are collected at four time points during the study period; baseline assessments are performed during the study entry until the administration of the first systemic therapeutic measure (T1 point). Systematic therapy includes cytotoxic chemotherapy, immunotherapy using an immune checkpoint inhibitor or targeted therapy using a tyrosine kinase inhibitor. These factors include stratification factors (cytotoxic chemotherapy or immunotherapy/targeted therapy). Subsequent assessment points occur at 4 ± 2 (T2 point), 8 ± 2 (T3 point) and 12 ± 2 (T4 point) weeks after randomization. After the T4 point, follow-up assessments including the determination of the modified Katz index score are performed at 8 ± 4-week intervals. In the control group, exercise and nutritional assessments are performed at the T1 and T4 assessment points. In this group, interventions are not performed at any assessment point. In the intervention group, exercise and nutritional interventions are performed at the T1-T4 points.

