#### Physical and exercise assessment

The physiotherapists assess the handgrip strength and short physical performance battery (SPPB) score according to the study protocol. The medical doctor, physiotherapist or nurse administers the lifestyle questionnaire in an interview and educates the participant about lifestyle measures needed to ensure their safety and to maintain the prescribed amount of physical activity. The lifestyle questionnaire includes information about the family structure, occupational status, the amount of physical activity on a usual day, routine habits and housework, participation in sports or exercise, frequency of going out, and experiences of falls. Physical activity is measured using an accelerometer (Lifecorder®, Suzuken Co. LTD., Nagoya, Japan) at the protocol-defined assessment intervals. The QOL assessments are performed at T1 and T4 using the EORTC-QLQ-C30 questionnaire.

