### Study objectives

The primary endpoint and secondary endpoints are listed in Table 3. The primary endpoint of this study is the disability-free survival. This endpoint is defined as the period from random assignment to the date of patients being evaluated as needing care based on the modified Katz index or death due to any cause. Overall survival is defined as the period from random assignment to the date of death due to any cause. Lean body mass (LBM) is one of the secondary endpoints. We use the lumber skeletal muscle mass index to analyze electronically stored CT images to estimate the LBM.

**Table 3 Tab3:** Endpoints for the trial

Primary endpoint	
The disability-free survival	
Secondary endpoint	
1) Lean body mass assessed by CT	
2) Physical function assessed by the hand-grip strength, SPPB score and physical activity measured by accelerometer	
3) Nutritional status assessed by body weight, MNA score and ingested nutritional quantity	
4) Quality of Life assessed by EORTC-QLQ-C30	
5) The proportion of patients treated with subsequent chemotherapy	
6) Overall survival, Progression free survival	
7) The cumulative number of days of hospitalization	
8) Activity of daily life	
9) Safety	

*CT* computed tomography, *SPPB* short physical performance battery, *MNA* Mini Nutritional Assessment, *EORTC-QLQ* The European Organization for Research and Treatment of Cancer Quality-of Life Questionnaire

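### Table 2 schedules control-arm physical activity at T1 only, while the text puts control exercise assessments at T1 and T4; the accelerometer endpoint depends on which is followed

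*Protocol article*

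**What the plan says.** The protocol article states the control arm's schedule twice.

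- **Table 2 (Assessments and interventions), exercise session, assessments.** The row "Assessment of physical activity (Physical activity measurement, Physical activity interview" has a mark for control at T1 and dashes at T2/T3 and T4. The intervention arm has marks at T1, T2/T3 and T4.
- **Time points of assessments and interventions.** "In the control group, exercise and nutritional assessments are performed at the T1 and T4 assessment points". No exception is made for physical activity.

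Three other places bear on the point.

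- **Table 3 (Study objectives)** lists as secondary endpoint 2: "Physical function assessed by the hand-grip strength, SPPB score and physical activity measured by accelerometer".
- **Aim of the NEXTAC-TWO study** hypothesizes that the interventions "will help maintain physical activity levels in elderly patients with advanced cancer who are at high risk of cachexia".
- **Physical and exercise assessment** says that the accelerometer is used "at the protocol-defined assessment intervals" and names no arm.

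**The concern.** A secondary endpoint of a randomized trial needs a follow-up value in both arms. Under Table 2, accelerometer activity has one in the intervention arm only.

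The estimate left would be the change over 12 weeks in treated patients. Those weeks coincide with the start of first-line therapy for advanced lung or pancreatic cancer, when disease and treatment can also change activity. Without a concurrent control value, the programme's contribution cannot be separated from theirs. The phase I study already measured activity by accelerometer in a single arm, so on this endpoint randomization would add nothing.

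This is not a detail left to the analysis plan. The article gives the schedule in two places and they disagree, and no analysis can recover measurements that were never taken.

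**Working it through.** The plan gives no figure to reproduce here. The check is a cell-by-cell reading of Table 2 against the text, followed by a rough count of the patients concerned.

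**1. Is the row intact?** It has six cells, three per arm, like the rows around it. Nothing suggests that a mark was lost when the table was read.

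**2. How do the other assessment rows treat the control arm?**

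| Table 2 row | Control T1 | Control T2/T3 | Control T4 |
|---|---|---|---|
| Food intake | yes | no | yes |
| Nutritional status (MNA) | yes | no | yes |
| Nutritional checklist | yes | no | yes |
| Skeletal muscle analysis | yes | no | yes |
| Grip strength and SPPB | yes | no | yes |
| EORTC-QLQ-C30 | yes | no | yes |
| **Physical activity** | **yes** | **no** | **no** |
| Diet and exercise diaries | no | no | no |

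The diaries belong to the intervention and feed no Table 3 endpoint. Physical activity is therefore the only Table 2 row feeding a Table 3 endpoint that lacks a control T4 mark.

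**3. Do the two schedules agree?** Table 2 files physical activity among the exercise-session assessments. Read plainly, the text's statement about control exercise assessments covers it. Post-baseline activity time points are then:

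- control arm by Table 2: 0;
- control arm by the text: 1 (T4);
- intervention arm by Table 2: 3 (T2, T3, T4).

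The sentence on accelerometer timing does not settle the matter, because it refers back to whatever schedule the protocol defines.

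**4. How many patients are concerned?** With 130 patients allocated 1:1, there are 130 / 2 = 65 per arm. Assume exponential disability-free survival with the planning medians of 8 and 12 months. The proportion event-free at time t is then 2^(−t / median). Week 12 is 84 / 30.44 = 2.76 months.

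- Control: 2^(−2.76/8) = 0.787; × 65 = 51 patients.
- Intervention: 2^(−2.76/12) = 0.853; × 65 = 55 patients.

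T4 has a window of ±2 weeks. At week 10 (2.30 months) the counts are 0.819 × 65 = 53 and 0.876 × 65 = 57. At week 14 (3.22 months) they are 0.757 × 65 = 49 and 0.830 × 65 = 54.

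So roughly 49 to 53 control patients would be event-free at T4. Under Table 2, none of them supplies an activity value.

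**The case against.** A reader of Table 2 alone might infer that the endpoint has no control data at all, that the investigators chose not to measure controls, and that the trial's stated mechanism therefore goes untested. The documents do not support any of these.

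- **No control data.** The text on time points, read plainly, provides a control T4 measurement. Control T1 data exist on either reading, and both arms wore the device before randomization: "Patients who demonstrated their ability to wear and handle the accelerometer for at least 4 days are enrolled and randomized".
- **A deliberate choice.** All comparable rows have a control T4 mark, which fits a slip in one cell at least as well as a decision.
- **Stated mechanism.** The Aim section gives maintained activity as a hypothesis. Its next sentence makes survival without disability the trial's question, and nothing in the article calls accelerometer activity the mechanism.

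It can also be said that sites work from the full protocol and the standardized manuals, not from a journal article. That is fair: what the site schedules contain is not shown, so harm in the field is possible but not demonstrated. The patient counts likewise describe what a T4 measurement could yield; they do not show a loss that has occurred.

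Finally, only one of three measures within one of nine secondary endpoints is involved. Grip strength and SPPB are scheduled for control at T1 and T4 in both places.

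These points limit the finding. They do not remove it: the two schedules still disagree, and the endpoint can be compared between arms at follow-up only under one of them.

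**Conclusion.** The contradiction is established. Table 2 gives the control arm no physical activity assessment after T1; the section on time points gives it one at T4.

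The consequence is conditional. If sites follow Table 2, control follow-up values number 0 of about 65, no between-arm comparison of follow-up activity or change is possible, and the hypothesis about maintained activity cannot be tested on this measure. If sites follow the text, the comparison stands and only the table needs correcting.

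Severity is moderate: this is an internal inconsistency affecting part of one secondary endpoint. Disability-free survival, its sample size and the other physical-function measures are untouched. The figure of about 51 control patients event-free at T4 rests on exponential survival at the planning medians. The number with usable data would also depend on how many wear the device.

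**What to change.** 1. Reconcile the two passages by marking the control T4 cell for physical activity in Table 2, as the section on time points implies. State that the same device and the same wear period apply in both arms. The row combines the accelerometer measurement with an interview; the endpoint needs the accelerometer part.
2. Confirm which schedule the full protocol and the site materials contain. If they differ or are unclear, send sites a clarification. The article reports recruitment as ongoing in February 2019 and expected to finish in July 2020, so many control T4 visits could still be captured.
3. If control T4 values were not collected for some patients, report the between-arm comparison as incomplete, with the number missing. Do not present the intervention-arm change as an efficacy result.

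The cost is one table cell and, if needed, a site memo. Control patients already attend T4 for other assessments and learned to use the device in screening, so the added burden is one further wear period.

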#### Time points of assessments and interventions

Exercise and nutritional assessment data are collected at four time points during the study period; baseline assessments are performed during the study entry until the administration of the first systemic therapeutic measure (T1 point). Systematic therapy includes cytotoxic chemotherapy, immunotherapy using an immune checkpoint inhibitor or targeted therapy using a tyrosine kinase inhibitor. These factors include stratification factors (cytotoxic chemotherapy or immunotherapy/targeted therapy). Subsequent assessment points occur at 4 ± 2 (T2 point), 8 ± 2 (T3 point) and 12 ± 2 (T4 point) weeks after randomization. After the T4 point, follow-up assessments including the determination of the modified Katz index score are performed at 8 ± 4-week intervals. In the control group, exercise and nutritional assessments are performed at the T1 and T4 assessment points. In this group, interventions are not performed at any assessment point. In the intervention group, exercise and nutritional interventions are performed at the T1-T4 points.

